#### Sample size estimation

According to the study purposes, a superiority design was considered appropriate. Our hypothesis is that the relapse rate in group A (triple therapy group) will be lower than that in group C (MTX monotherapy group) in 60 weeks after randomization.

Sample size was calculated by PASS 11.0. It was reported that for patients with established RA achieving CR or LDA by TNFi combined with MTX, 24% to 85% suffered from disease relapse after discontinuation of TNFi [4–7]. When combined csDMARDs preserved after TNFi removed, the rate of relapse was 51.2–58% [4, 7]. We assume that adding HCQ + SSZ 3 months before the removal of TNFi may somehow decrease the relapse. Accordingly, we expect the relapse rate as 50% in patients in triple therapy group, and 74% in MTX monotherapy group. With a power of 0.8 and a significance level of 0.05 (two-sides), using a 1:1:1 treatment allocation of enrollment, to detect the difference of relapse rate between the two groups, the required sample size is 61 for each group. Given the estimated dropout rate of 20%, we intend to recruit a total of 240 subjects (80 for each group).

We assume that the relapse rate may be similar between group A and group B (TNFi maintenance therapy group), and the cost-effectiveness may be better in group A than in group B. The relapse rate and cost-effective comparison between group A and group B will be exploratory and there was no relevant research hypothesis, so the sample size was not calculated by it.

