Pharmaceutical economics analysis will be performed. Base case analysis and sensitivity analysis will be performed by decision tree model based on Per-Protocol Set (Fig. 2). A series of one-way deterministic sensitivity analysis will be conducted. For the cost-effectiveness analysis, the proportion of not relapse will be taken as effectiveness. The direct cost (medical expenses), indirect cost (productivity lost), total cost (the total of direct and indirect cost), and average cost/effectiveness ratio of each treatment strategy will be calculated. Direct cost will include the cost of experimental drugs, laboratory and radiology examinations, AE/SAE treatment, traffic expenses and accommodation fees directly related with follow-up visit. Indirect cost will include loss of income due to the patients’ and their family’s inability to work due to RA. The incremental cost effectiveness ratio (ICER) of group A and group B against group C will be calculated. Cost-utility analysis will be performed by using EQ-5D-5L and SF-6D as utility index. The costs and average cost/utility ratio of each treatment strategy will be calculated. The incremental cost utility ratio [the cost of increase 1 quality adjusted life year (QALY)] of group A and group B against group C will be calculated. The treatment strategy will be considered to have cost-utility if the incremental cost utility ratio is below 3 times of China’s per capita GDP in the past year (¥100,000).

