**Fig. 2 Fig2:**
[figure not shown]
The decision tree model of the study. RA: Rheumatoid Arthritis; MTX: methotrexate; HCQ: hydroxychloroquine; SSZ: sulfasalazine

Non-parametric bootstrap will be used to calculate the 95% confidence interval of incremental cost effectiveness ratio and draw the cost-effectiveness acceptability curve. The factors which may affect the analysis results will be evaluated by one-way and probability sensitivity analysis. All the analysis will be performed by TreeAgePro11.0 software.

Safety analysis will be performed based on the safety set (SS). The incidence of AEs and SAEs related to the study will be described. Crosstabs will be constructed to map the changes of laboratory index.

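### The cost-utility rule checks only that the ratio is below the threshold, so as written a strategy with higher cost and fewer QALYs than group C would pass

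*Protocol article*

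**What the plan says.** The economic part of the Statistical analysis section (protocol article) sets up the ratio and then the verdict. The ratio is introduced as "The incremental cost utility ratio [the cost of increase 1 quality adjusted life year (QALY)] of group A and group B against group C". The next sentence gives the rule: "The treatment strategy will be considered to have cost-utility if the incremental cost utility ratio is below 3 times of China’s per capita GDP", taken for the past year, with ¥100,000 in brackets.

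Uncertainty is handled after Fig. 2: "Non-parametric bootstrap will be used to calculate the 95% confidence interval of incremental cost effectiveness ratio and draw the cost-effectiveness acceptability curve". One-way and probabilistic sensitivity analyses are also planned. None of these is linked to the verdict. The section has no dominance clause, no condition on the sign of the cost or QALY difference, and no net-benefit form.

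**The concern.** A ratio loses the signs of its two parts. A strategy that is dearer and worse can have the same negative ratio as one that is cheaper and better, and both lie below a positive threshold. When both differences are negative the ratio is positive, but it then measures the saving per QALY lost, where larger is better, so the inequality should reverse. The rule is safe only when the QALY difference is positive.

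The situation could arise in this trial. Under Interventions, group B receives 48 more weeks of TNFi than group C, and the Background describes csDMARDs as much cheaper than biologics, so a positive cost difference for B against C is likely. QALY differences may be small: the Discussion cites an earlier trial of infliximab plus MTX against triple therapy that found no statistically significant difference in QALY gain. That is not the contrast judged here, but it shows that an estimate near zero, whose sign chance can flip, is realistic. At stake is a published yes/no statement that could endorse a strategy that is both dearer and less effective.

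**Working it through.** **Inputs.** The rule and the comparisons (A against C, B against C) come from the Statistical analysis section. The threshold λ is run at ¥100,000 and ¥300,000, because the bracketed figure can be read as three times GDP per head or as GDP per head itself. The number per arm is 61, from Sample size estimation. The article gives no cost or QALY differences, SDs or correlation, so all of those below are assumptions.

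**The plan's own figure.** The article states no error rate for the cost-utility rule. Its 61 per group does reproduce: (1.960 + 0.842)² × [0.50 × 0.50 + 0.74 × 0.26] / 0.24² = 60.28, so 61.

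**Step 1: the signs.** Let ΔC and ΔQ be the cost and QALY differences against group C. The written rule is ΔC/ΔQ < λ. The sign-safe form is net monetary benefit NMB = λ × ΔQ − ΔC > 0.

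| ΔC (¥) | ΔQ | Ratio (¥/QALY) | Written rule, either λ | NMB, λ = ¥100,000 | NMB, λ = ¥300,000 |
|---|---|---|---|---|---|
| +20,000 | −0.05 | −400,000 | passes | −25,000 | −35,000 |
| −20,000 | +0.05 | −400,000 | passes | +25,000 | +35,000 |
| +20,000 | +0.05 | +400,000 | fails | −15,000 | −5,000 |
| −2,000 | −0.05 | +40,000 | passes | −3,000 | −13,000 |
| −20,000 | −0.05 | +400,000 | fails | +15,000 | +5,000 |

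Rows 1 and 2 are opposite outcomes with the same ratio and the same verdict. In rows 4 and 5 the QALY loss is the same, yet the rule accepts the smaller saving and rejects the larger. Row 3, where QALYs rise, is judged alike by both forms.

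**Step 2: how often, when the strategy surely costs more.** Suppose ΔC > 0 in effectively every sample and the estimate ΔQ is symmetric about a true value of 0. Then

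P(pass) = P(ΔQ < 0) + P(ΔQ > ΔC/λ) = 0.5 + P(ΔQ > ΔC/λ) ≥ 0.5,

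whatever the correlation between cost and QALYs.

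**Step 3: illustration.** True ΔQ = 0, 61 per arm, assumed per-patient SDs of 0.15 QALY and ¥20,000, no correlation, 1,000,000 draws. The standard errors are 0.15 × √(2/61) = 0.0272 QALY and 20,000 × √(2/61) = ¥3,621.

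| True ΔC (¥) | λ (¥) | Written rule passes | NMB > 0 |
|---|---|---|---|
| 0 | 100,000 | 70.4% | 50.0% |
| 5,000 | 100,000 | 60.1% | 13.4% |
| 20,000 | 100,000 | 50.0% | <0.1% |
| 0 | 300,000 | 86.6% | 50.0% |
| 5,000 | 300,000 | 77.3% | 28.6% |
| 20,000 | 300,000 | 51.2% | 1.2% |

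At ¥20,000 and λ = ¥100,000, essentially every pass is a sample in which the strategy was dearer and worse.

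**Step 4: when the sign of the cost difference is not certain.** If both true differences are 0 and cost and QALY correlate at ρ, with r = SD(cost)/SD(QALY),

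P(pass) = 0.5 + arctan[(λ − ρr) / (r√(1 − ρ²))] / π.

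Take SDs of 0.15 QALY and ¥60,000, so r = 400,000:

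- λ = ¥100,000, ρ = 0.5: (100,000 − 200,000)/(400,000 × 0.866) = −0.289, giving 41.1%.
- λ = ¥300,000, ρ = 0.9: 39.5%.
- λ = ¥100,000, ρ = −0.5: 72.7%.

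The rate can therefore fall on either side of one half.

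**The case against.** The strongest reply is that the preceding sentence describes the ratio as the cost of one more QALY, which presupposes a gain; a dominated strategy has no such cost and would not be declared. This is a fair reading of intent. With ΔQ > 0 required, the pass rates in Step 3 drop to 35.2%, 11.7% and <0.1% at ¥100,000, and to 43.3%, 28.0% and 1.2% at ¥300,000. But the description labels the ratio. It does not restrict the verdict, the ratio is to be calculated for A and B without exception, and nothing says what follows if QALYs fall.

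A second reply is that an article leaves such detail to the full protocol or analysis plan. That would answer a missing rule. Here the article prints a complete yes/no rule whose form gives wrong verdicts. The bootstrap and acceptability curve would help to reveal a dominated result but do not decide the verdict.

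Third, a QALY loss for A would run against the planning assumption ("we expect the relapse rate as 50% in patients in triple therapy group, and 74% in MTX monotherapy group"). The planned costs also include productivity loss and adverse-event treatment, so A might even cost less than C. This stands: the problem may never arise for A. It is a reason not to predict a wrong verdict, but not a reason to keep the rule.

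Fourth, the simulation uses normal mean differences, not the planned decision tree on the per-protocol set. This also stands; the percentages are illustrations, while the sign results in Step 1 need no model.

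**Conclusion.** The point holds. As written, the rule passes a dearer, less effective strategy and reverses the proper order among cheaper, less effective ones. That follows from the arithmetic at either reading of the threshold. The rate of at least one half rests on two conditions: the strategy surely costs more, and there is no true QALY difference.

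Two stronger readings are not supported:

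- A reader might infer that the rule passes at least half the time whenever there is no effect. Step 4 gives counterexamples near 40%, and the article supplies no SDs or correlation from which to settle a rate. When cost and QALYs both truly do not differ, net monetary benefit above 0 itself passes 50.0% of the time.
- A reader might infer that the rule prefers harm to worthwhile benefit. With 80 per arm, a QALY SD of 0.20, a cost SD of ¥10,000, a true extra cost of ¥30,000 and λ = ¥300,000, it passes 83% of the time for a 0.03 QALY loss and 19% for a 0.03 gain. But that gain costs 30,000/0.03 = ¥1,000,000 per QALY, so rejecting it is correct. Only the 83% is a fault.

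The importance is limited. The economic outcome listed under Study outcomes is the cost per relapse avoided, and cost-utility is a further secondary analysis. The primary relapse comparison and the sample size are unaffected.

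**What to change.** Replace the rule sentence with wording such as: *A strategy will be considered to have cost-utility against group C if its incremental net monetary benefit (threshold × QALY difference − cost difference) is greater than 0. A strategy with higher cost and fewer QALYs will be reported as dominated, without cost-utility; one with lower cost and more QALYs as dominant. Where both differences are negative, the ratio will be reported as the saving per QALY lost, and the strategy qualifies only if that saving exceeds the threshold.*

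Keeping the ratio is equivalent if the threshold is applied as now only when the QALY difference is positive and the other cases are handled as above. Both forms agree with the present rule whenever QALYs rise. The verdict should be read with the planned acceptability curve, since a point-estimate rule carries no statement of uncertainty.

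The cost is a few lines of text, with no new data, visits or patients. The downside is that a strategy the present rule would pass may no longer qualify.

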**Fig. 2 Fig2:**
[figure not shown]
The decision tree model of the study. RA: Rheumatoid Arthritis; MTX: methotrexate; HCQ: hydroxychloroquine; SSZ: sulfasalazine

Non-parametric bootstrap will be used to calculate the 95% confidence interval of incremental cost effectiveness ratio and draw the cost-effectiveness acceptability curve. The factors which may affect the analysis results will be evaluated by one-way and probability sensitivity analysis. All the analysis will be performed by TreeAgePro11.0 software.

Safety analysis will be performed based on the safety set (SS). The incidence of AEs and SAEs related to the study will be described. Crosstabs will be constructed to map the changes of laboratory index.

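### The bootstrap 95% interval of the ICER is planned without requiring that the effect difference be clear of zero; at the design's own relapse rates it has no valid finite form in about 10% to 20% of trials.

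*Protocol article*

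**What the plan says.** The economic analysis is described in the Statistical analysis section of the protocol article. The effect measure is fixed: "For the cost-effectiveness analysis, the proportion of not relapse will be taken as effectiveness". The contrasts are fixed too: "The incremental cost effectiveness ratio (ICER) of group A and group B against group C will be calculated". A cost-utility ratio follows for the same contrasts, in the sentence that begins "The incremental cost utility ratio [the cost of increase 1 quality adjusted life year (QALY)] of group A and group B against group C will".

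Uncertainty is covered after Fig. 2: "Non-parametric bootstrap will be used to calculate the 95% confidence interval of incremental cost effectiveness ratio". The same sentence also plans an acceptability curve from that bootstrap. The one after it adds: "The factors which may affect the analysis results will be evaluated by one-way and probability sensitivity analysis". The interval is named for the cost-effectiveness ratio; the text does not say whether the cost-utility ratio gets one as well. It sets no condition on the denominator and does not say how replicates with a zero or negative effect difference are treated.

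The section Sample size estimation supplies the design rates: "we expect the relapse rate as 50% in patients in triple therapy group, and 74% in MTX monotherapy group".

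**The concern.** The ICER is a cost difference divided by an effect difference. While the effect difference is clearly positive, the ratio is a continuous, ordered quantity and an interval for it has a plain meaning. Once the data are compatible with an effect difference of zero, the ratio runs off to plus or minus infinity. A negative value may then mean cheaper and better, or dearer and worse. Percentiles of the sorted replicates will still produce two numbers, but those numbers no longer bound the ratio at the 95% level.

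The cost per relapse avoided is a listed secondary outcome. The plan commits to an interval for it whatever the data show, and in an unlucky trial the published limits could not be interpreted.

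**Working it through.** **Inputs from the protocol article (Sample size estimation).** Relapse 50% in A and 74% in C, two-sided alpha 0.05, power 0.80, 61 required per group, 80 recruited per group, 20% dropout. The economic model uses the Per-Protocol Set, so fewer than 80 per arm is realistic: 80 × 0.8 = 64.

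**Reproducing the plan's figure.** With unpooled variance, n = (1.960 + 0.842)² × (0.50×0.50 + 0.74×0.26) / 0.24² = 60.3, so 61 per group. This agrees with the document.

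**Relapse denominator, A versus C.** The difference is d = 0.74 − 0.50 = 0.24 and SE = √[(0.25 + 0.1924)/n]. The chance that the trial's 95% interval for d includes zero is Φ(1.96 − d/SE), the other tail being negligible. The average share of bootstrap replicates at or below zero is Φ(−d/(SE√2)), because replicates scatter around an estimate that itself scatters around d.

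| n per arm | SE | d/SE | Trials whose interval for d includes zero | Average share of replicates ≤ 0 |
|---|---|---|---|---|
| 80 | 0.0744 | 3.23 | 10% | 1.1% |
| 64 | 0.0831 | 2.89 | 18% | 2.1% |
| 61 | 0.0852 | 2.82 | 20% | 2.3% |

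The 20% at n = 61 is the complement of the planned 80% power. Simulating binomial trials gives 11%, 18% and 21%. If B relapses at the same rate as A, as the protocol supposes, the figures for B versus C are the same.

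The two right-hand columns answer different questions. The average share is small because most trials have almost no replicates below zero. The column before it counts the trials in which the ratio interval fails.

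**Sign of the cost difference.** The document gives no cost figures. With d positive, replicates may lie in the dearer-and-better or the cheaper-and-better quadrant. The ratio passes smoothly through zero between them, so a negative limit simply means cost saving. This does not invalidate the interval.

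**QALY denominator, if the same interval were used there.** The document gives no QALY gain or SD. Assume SD 0.12 and n = 80, so SE = 0.12 × √(2/80) = 0.0190, and vary the gain:

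| Assumed gain | gain/SE | Average share of replicates ≤ 0 |
|---|---|---|
| 0.02 | 1.05 | 23% |
| 0.05 | 2.64 | 3% |
| 0.10 | 5.27 | about 0% |

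**What failure looks like.** Keep SD 0.12 and n = 80. Assume also a cost SD of ¥15,000 (SE = 15,000 × √(2/80) = ¥2,372) and independent normal differences. Centre the replicates on two opposite results.

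- Gain of 0.02 QALY and saving of ¥2,000: percentile interval of the ratio about −¥1.3 million to +¥1.1 million.
- Loss of 0.02 QALY and extra cost of ¥2,000: again about −¥1.3 million to +¥1.1 million.

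Incremental net benefit separates them. At ¥100,000 per QALY it is 0.02 × 100,000 + 2,000 = ¥4,000 in the first case and −¥4,000 in the second. Its SE is √(1,897² + 2,372²) = ¥3,037, and 4,000/3,037 = 1.32. So 91% of values are positive in the first case and 9% in the second.

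**The case against.** The strongest reply is that the plan already holds the remedy. The sentence that announces the interval also announces an acceptability curve. That curve comes from the same replicates by way of net benefit and is valid in all four quadrants. Sensitivity analyses follow. A reader of the interval clause alone might infer that the ratio interval is the only planned measure of uncertainty; the full sentence shows otherwise. This stands, and it limits the harm. It does not make the interval valid in the trials where it fails.

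A second reply is that the relapse ICER is mostly safe. A reader might infer that replicates will probably scatter over several quadrants and mix dominant with dominated results. For the relapse ratio at the planned size the document's figures do not support that: on average only 1% to 2% of replicates have a non-positive denominator, and a change in the sign of cost is harmless. The 10% to 20% of trials in which zero is not excluded remain.

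Third, the QALY case is conditional twice over: the interval is not announced for that ratio, and the size of the problem turns on an assumed gain. Both parts stand. Nor can the point be built on A versus B, where similar relapse would put the denominator near zero, because no ratio is planned for that contrast and it is declared exploratory.

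Last, interval type and the handling of replicates may be left to a fuller document. That is fair for such detail. But an unconditional interval for a ratio is a method the article states, not one it leaves open.

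**Conclusion.** The concern holds in a limited form. The plan fixes a bootstrap 95% interval for the ICER with no requirement that the effect difference be distinguishable from zero. At the design rates that requirement fails in about 10% of trials at 80 per arm and 18% to 20% at 64 to 61 per arm, and the ratio then has no valid finite 95% interval. In the remaining 80% to 90% the interval can be read.

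These figures rest on the protocol's 50% and 74% and a normal approximation; a smaller true difference would raise them. For cost per QALY the risk may be greater, with 23%, 3% or about 0% of replicates at or below zero for assumed gains of 0.02, 0.05 or 0.10. The document does not show which applies, so a QALY interval likely to fail is a possibility and not a finding.

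**What to change.** Use the same bootstrap replicates and change what is reported:

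- Give incremental net monetary benefit with a bootstrap 95% interval for A versus C and B versus C. For QALYs use the threshold in the Statistical analysis section; for relapse avoided use a stated range of willingness-to-pay values.
- Show the cost-effectiveness plane with the share of replicates in each quadrant.
- Keep the acceptability curve.
- Give the ICER as a point estimate, with an interval for the ratio only when the 95% interval of the effect difference excludes zero.

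This needs a few sentences in the analysis plan before the data are analysed and no further data. The costs are that a willingness-to-pay range per relapse avoided must be chosen and defended, and that there is slightly more to report.

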## Methods/design

### Study design

This will be a two-stage study. The first stage will serve as an induction treatment with TNFi plus MTX for no more than 12 weeks. Patients who have achieved CR or LDA [defined as disease activity score 28 (DAS28)-CRP ≤ 3.2] in 12 weeks will enter the second stage at the time of CR/LDA achieved. The second stage will be a multiple-center, randomized, outcome assessment blinded, parallel controlled clinical trial. All eligible participants will be randomly allocated to three arms at a ratio of 1:1:1 to receive different treatment strategies for 60 weeks or until relapse.

This study will be expected to be conducted from October 2015 to September 2022. The first patient was recruited on Oct 8, 2015 and the last patient is planned to be recruited by Sep 30, 2021. The study flow-chart is shown in Fig. 1.

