### Study outcomes

The primary outcome will be disease relapse, which is defined as DAS28-CRP increases by at least 0.6 compared with that at randomization and is greater than 3.2 simultaneously.

The secondary outcomes will include the following: the incremental cost per reducing 1 case of relapse; change of disease activity score from baseline, assessed by DAS28-CRP, DAS28-ESR, CDAI and SDAI, at 60 weeks after randomization; duration of maintaining CR or LDA after randomization; change of hands X ray modified Sharp score at 60 weeks after randomization; ultrasound remission of hands at 60 weeks after randomization; Health Assessment Questionnaire Disability Index (HAQ-DI) and health related quality of life [the five-levele EuroQol-5D-5L (EQ-5D-5L) and short form-6D (SF-6D)] at 60 weeks after randomization; adverse events and complications; and patient reported outcomes (PRO) including rash, nausea, vomiting, diarrhea, abdominal pain and fever.

All outcomes will be measured after 60 weeks.

Responsible physicians will monitor and record any adverse events (AEs) during the whole trial. Expected AEs will include: allergy; ALT and AST elevation; hemocytopenia; infection; digestive tract symptom including nausea and vomiting; and hemorrhage of digestive tract defined by fecal occult blood positive, etc. In case of AEs, symptomatic treatment or reduction of drug dosage or even discontinuation of drugs will be carried out when necessary. If the drugs is tapered or discontinued, a serious AE will be considered and the patient should exit the study. Physicians will assess the association between intervention and AEs on a 6-point scale (1 = definitely related; 2 = probably related; 3 = possibly related; 4 = probably not related; 5 = definitely not related; 6 = unknown). All AEs will be categorized into three levels using the Spilker classification [(1) mild = not need additional intervention, nor significantly inhibit normal life function of the participant; (2) moderate = significantly inhibit the normal life function of the participant, and may need additional intervention, recovering afterwards; and (3) severe = require intensive intervention, and leave sequelae).

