Serious adverse event (SAE) is defined as any of the following conditions: (1) threat to life; (2) lead to hospitalization or extend hospital stay; (3) lead to permanent or notable disability or functional disorder; and (4) lead to taper or discontinue the study drugs. In case of SAE or scheme violation during study duration, the relevant Institutional Review Board (IRB) and the leading study site (Peking University First Hospital) will be informed and will decide whether the trial will continue or not. Patients will be followed even if protocol has been breached for any reason. The SAE will be recorded as safety outcome.

An independent assessment committee will be set up for outcomes evaluation. The assessment committee will be blinded to the treatments. However, in case of “SAE”, unblinding will be permitted.

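### The only AE/SAE incidence summary is worded as restricted to related events, which does not match the unrestricted safety outcomes defined elsewhere in the protocol

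*Protocol article*

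**What the plan says.** The safety paragraph that closes the Statistical analysis section (after Fig. 2) has three elements. The analysis uses the safety set. For events, "The incidence of AEs and SAEs related to the study will be described". For laboratory data, "Crosstabs will be constructed to map the changes of laboratory index".

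The Study outcomes section is wider. On collection: "Responsible physicians will monitor and record any adverse events (AEs) during the whole trial". Its list of secondary outcomes includes "adverse events and complications; and patient reported outcomes (PRO) including rash, nausea, vomiting, diarrhea, abdominal pain and fever". The same section defines SAEs and counts them as a safety outcome. None of these statements carries a relatedness condition.

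On causality, Study outcomes says: "Physicians will assess the association between intervention and AEs on a 6-point scale". The levels run from definitely related (1) to definitely not related (5), with 6 for unknown.

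On blinding, Study design calls the second stage a "randomized, outcome assessment blinded, parallel controlled clinical trial", and Study outcomes adds: "The assessment committee will be blinded to the treatments". No blinding of treating physicians or patients is stated.

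**The concern.** The protocol collects every adverse event and names adverse events as an outcome, yet the one incidence summary it commits to is worded for a subset. An analysis plan that follows the sentence would inherit the restriction.

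The subset matters because of who would define it. Relatedness is rated by physicians, and blinding is stated only for the assessment committee. Under Interventions, two oral drugs start at randomisation in group A alone, while groups B and C continue drugs already taken during induction. A physician who knows this may more readily call an event related in group A. A summary filtered in that way can show a difference that reflects attribution, or conceal one that is real.

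Safety is in the trial's title. The Discussion states the aim as evaluating safety, among other things, against both comparator groups, so the incidences will be read across arms even though the paragraph only describes them.

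**Working it through.** **1. The statements side by side**

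| Item | Where | Relatedness condition? |
|---|---|---|
| Recording of AEs | Study outcomes; AE row of Table 1 | No |
| AEs and complications as a secondary outcome | Study outcomes | No |
| SAEs as a safety outcome | Study outcomes | No |
| Patient-reported symptoms | Study outcomes | No |
| Laboratory crosstabs | Statistical analysis | No |
| Incidence of AEs and SAEs | Statistical analysis | Yes, as worded |

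Only the last row is restricted, and it is the only incidence summary given for AEs and SAEs.

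**2. What the qualifier could mean**

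- (a) It restricts both AEs and SAEs to those judged related.
- (b) It restricts only the SAEs.
- (c) It loosely means events arising during the study.

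Under (a) or (b) an attribution filter reaches at least the SAEs, and the summary departs from the outcome definition. Under (c) the intention is sound but the sentence does not express it. The text does not link the qualifier to the 6-point scale, so it cannot settle which is meant.

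**3. Are the rating physicians open-label?** This is not stated, but it follows from the design. Only the committee is said to be blinded. No placebo or dummy is described. Group A takes added oral drugs, and groups A and C stop TNFi after 12 weeks (Interventions). TNFi is injected on site by staff (Discussion).

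**4. Possible size under reading (a)**

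The plan states no expected AE incidence and no attribution rate, so there is no figure of its own to reproduce. All inputs here are assumptions.

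Let p be the true proportion of patients with an AE, equal in two arms, and let a and b be the proportions judged related in each arm. Then the reported incidences are p × a and p × b, and the spurious gap is p × (a − b).

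| p | 60% vs 50% | 60% vs 40% | 70% vs 40% |
|---|---|---|---|
| 20% | 12% vs 10%: 2 points | 12% vs 8%: 4 points | 14% vs 8%: 6 points |
| 40% | 24% vs 20%: 4 points | 24% vs 16%: 8 points | 28% vs 16%: 12 points |
| 60% | 36% vs 30%: 6 points | 36% vs 24%: 12 points | 42% vs 24%: 18 points |

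The unfiltered incidence shows a gap of 0 in every cell.

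Masking works the same way. With true incidences of 40% and 60%, and attribution of 60% and 40% respectively, the reported figures are 0.40 × 0.60 = 24% and 0.60 × 0.40 = 24%. A real 20-point difference disappears.

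The formula treats each affected patient as having one event, or attribution as made once per patient. If a patient with several events counts whenever any one of them is judged related, the reported levels and the gap both change.

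**The case against.** The strongest reply is that this is loose wording in a condensed article. The sentence says related to the study, whereas the 6-point scale rates association with the intervention, and the two are never connected. The phrase may attach only to SAEs, or mean no more than events during the study. This stands: that events rated unrelated or unknown will be dropped is one reading, not an established fact.

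A reader might go further and infer that the whole safety evaluation rests on open-label attribution. The document does not support that. Laboratory crosstabs need no causal judgement, and they bear on transaminase elevation and hemocytopenia, two of the expected AEs. Patient-reported rash, nausea, vomiting, diarrhea, abdominal pain and fever need none either. These sources do not cover infections or SAEs in general, so part of the gap remains.

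A reader might also infer that a formal between-arm safety comparison is biased. The paragraph names no test or contrast; it plans description only. The problem lies in how the described incidences will be read.

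The absence of a cut-off on the 6-point scale is detail that a statistical analysis plan commonly supplies, and on its own it would not be a finding. It matters only because the protocol sentence appears to make relatedness the entry condition for the main summary. That sentence is stated text at odds with the protocol's own outcomes, so an unseen analysis plan does not remove the mismatch.

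**Conclusion.** The point holds in a limited form. Read literally, the AE/SAE incidence summary is narrower than the safety outcomes in Study outcomes, and the two sections need to be aligned. If the restriction means the causality rating, the summary depends on the judgement of physicians who are open-label by clear implication, though not by explicit statement. Attribution alone could then produce a gap of about 2 to 18 points when true incidence is equal, or hide a real difference. That range rests entirely on the assumed incidences and attribution splits and on one attribution per affected patient. It does not show that such bias will occur in this trial. The laboratory and patient-reported safety data are outside the problem. The correction is worth making because it resolves all three readings of the sentence at little cost.

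**What to change.** Replace the incidence sentence in the Statistical analysis section with wording to this effect:

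*The main safety summary will be the incidence of all AEs and all SAEs in the safety set, regardless of judged relationship to treatment. Randomised-stage events will be shown by arm and induction-stage events listed separately. Events judged related will be given in a supplementary table; the scale levels that count as related, and the handling of events rated unknown, will be fixed before database lock.*

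Listing induction events separately keeps them visible, since recording covers the whole trial, without assigning pre-randomisation events to an arm.

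The cost is one sentence and one extra table. No new data are needed, because Table 1 already has AEs recorded at every visit. The article reports the trial as ongoing, with 123 patients in the randomised stage, and the database is to be locked before it goes to the statistician, so the change can be made ahead of analysis. A protocol revision would follow the agreement and IRB steps described in the Discussion.
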